### 2.4. Endpoints and Assessment Procedures

Due to personal and financial resources, the blinding of assessors is not possible. This limitation provides a tolerable risk of bias. The same group of researchers assesses all measurements at baseline, interim and post-assessment. All measurements are conducted at the same laboratories with the same assessment tools at the German Sport University Cologne at the Department of Exercise Training and Sport Informatics (Intervention Research in Exercise Training) and the Institute of Cardiology and Sports Medicine. For each domain of assessment, an expert serves as a “gold-standard assessor” and instructs all other assessors about the measurement procedures. Accordingly, a standard operating procedure (SOP) can be assured throughout all measurements. T1, T2 and T3 are scheduled at the same time of the day if possible (at least morning and afternoon, respectively). Participants are asked to follow their usual daily routine on the testing day but without any strenuous exercise within 48h prior to testing. At T1, participants are tested with the MMSE for cognitive impairment and answer the “Freiburger Fragebogen zur körperlichen Aktivität” (FFB) [22] to assess baseline physical activity levels. Participant files are saved under non-personalized, pseudonymized identification numbers. A file for uncoding numbers is stored separately only accessible by the principal investigtor.

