The muscle architecture of the right VL is assessed on a participant in a supine position with the knee fully extended [30]. The foot is placed with the sole put against a wall, resulting in a rectangular position in the ankle joint. Landmarks of the VL are palpated (greater trochanter and lateral intercondylar notch) and marked with a dermographic pencil, the distance is considered as VL length. The distal 55% VL length is measured with a flexible tape measure. The operator then positions the probe perpendicularly to the main axis of the muscle at the marked 55% VL length. The medial and the lateral edges of the VL are identified by moving the probe medially and laterally along this plane. The full distance is measured and the 50% distance is marked on the skin. This point represents the center of the muscle belly at 55% VL length. Three different longitudinal images of the VL muscle are taken and saved for processing. Since the assessment of VL ultrasound is not yet well standardized in the literature, a second method is used to locate another region of the VL used by some other authors. Therefore, the greater trochanter and the tuberositas tibiae are used as landmarks, and the 50% distance is marked on the skin. Assessment of the medial and lateral edge and the subsequent steps is the same as mentioned above. Analysis of ultrasound images is performed with the free NIH Image-J software (Version 1.52a, U.S. National Institutes of Health, Bethesda, Maryland, MD, USA). Muscle thickness, fascicle length and pennation angle will be measured. 

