Furthermore, heart rates, heart rhythm and heart rate variability are documented using a 24 h electrocardiogram (ECG) (Langzeit-EKG, Amedtec, Aue, Germany). Blood pressure is documented over 24 hours every 30 minutes during the day and every 60 minutes during the night using a standard cuff (Mobil-O-Graph®, IEM, Stolberg, Germany).

A non-invasive retinal vessel analysis is conducted to measure retinal vessel diameters as microvascular biomarkers of cardiovascular risk using a fundus camera and a semi-automated software system (SCA-T, Imedos Systems UG, Jena, Germany). Three images of the right eye are taken at a 45° angle with the optic nerve at center. Arterioles and venules at a distance of 0.5–1 times the diameter of the optic nerve are semi-automatically analyzed (Vellelmap 2, Visualis, Imedos Systems UG, Jena, Germany). The high reliability of this method has been shown [38,39]. 

Echocardiography is performed by an experienced echocardiographer using the Vivid iq with a M5Sc 1.5-4.6 transducer (GE Healthcare Systems, Boston, MA, USA, 2018). The participant lies in a semi-supine resting position. Images are taken based on the recommendations of the American Society of Echocardiography (ASE) while the participant holds his breath [40]. Conventional echocardiography includes standard measurements of cardiac dimensions, contractility and diastolic function. Speckle tracking images for calculation of myocardial strain are recorded in apical three-chamber, two-chamber and four-chamber views for longitudinal values and in the parasternal short-axis at the level of papillary muscles for circumferential and radial values. Analysis of all images is conducted offline using EchoPac-Software (Version 202, GE Healthcare, Boston, MA, USA, 2018).

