### 3.3. Potential Limitations and Risk for Bias

Participants were recruited from the general population via newspaper advertisement, which could lead to a selective recruitment of those older adults, that are intrinsically motivated to exercise and wo are already physically active. Group allocation was done according to the minimization method, which is comparable to a randomization method in smaller samples [21]. It allows us to balance important demographic measures and primary and secondary outcomes with possibly small group differences at baseline. Sex, age, maximum knee extension strength, dual task gait speed and VO2peak serve as strata for minimization, notably attenuating the risk of bias. Only participants who stated that they were willing to be randomized in one of the two groups could take part in the study to minimize dropout in the control group. Group preferences were strictly not allowed. Couples were randomized to the same groups. As is usual in exercise intervention studies, the blinding of participants is not possible. Due to personal and financial resources, the blinding of assessors and coaches is not possible either, which yields an acceptable risk for bias. Measurements are standardized and performed in the same room by the same assessor at T1, T2 and T3. Measurements are scheduled at the same time of the day for T1, T2 and T3 if possible. For each measurement domain, one gold-standard setter teaches all other assessors. The control group does not receive any treatments, but for ethical reasons they receive written recommendations for physical activity. Their potential autonomous exercise over the one-year period could influence the results of the study and is, therefore, captured via a logbook.

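### The statement that assessors cannot be blinded makes no exception for stored ultrasound, echocardiographic and retinal images, which could be read masked even though live tests cannot

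*Protocol article*

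**What the plan says.** Section 2.4 states: "Due to personal and financial resources, the blinding of assessors is not possible". The next sentence gives the judgement on it: "This limitation provides a tolerable risk of bias". The same section says who measures: "The same group of researchers assesses all measurements at baseline, interim and post-assessment". Section 3.3 comes back to the limitation: "the blinding of assessors and coaches is not possible either, which yields an acceptable risk for bias". No outcome is exempted in either place.

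Three groups of secondary outcomes come from images:

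- **Muscle ultrasound (section 2.6.1).** Vastus lateralis images are saved for later processing, and muscle thickness, fascicle length and pennation angle are then measured: "Analysis of ultrasound images is performed with the free NIH Image-J software".
- **Echocardiography, including myocardial strain (section 2.6.3).** "Analysis of all images is conducted offline using EchoPac-Software".
- **Retinal vessel diameters (section 2.6.3).** Three fundus images are taken, and the vessels are then analysed semi-automatically in software.

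On coding, section 2.4 says: "Participant files are saved under non-personalized, pseudonymized identification numbers". The decoding file is kept separately, and only the principal investigator has access to it.

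**The concern.** A tester who meets the participant, gives instructions and encourages effort is hard to blind on a limited budget. A reader who places measurement points on a stored image is in a different position, because arm and visit can be hidden at that step. The plan treats both situations as one and calls the whole risk tolerable.

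Sections 1 and 3.1 state openly that gains from training are expected. A reader who shares that expectation and knows arm and visit can move operator-dependent readings in the expected direction without intending to. Section 2.6 says the secondary endpoints are there to help explain the mechanisms of adaptation. A between-arm difference in fascicle length or strain that arose partly at the reading desk would weaken that use, and this part of the bias can be avoided.

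**Working it through.** **1. Does the statement cover image reading?** Section 2.4 rules out assessor blinding without exception and assigns all measurements to one group of researchers. Section 3.3 repeats this for assessors and coaches. On a plain reading, image measurement is included.

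**2. Which image outcomes can be separated from acquisition?**

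| Outcome | What the article says about reading | Read after acquisition? |
|---|---|---|
| Echocardiography, strain | Analysed offline | Stated |
| Muscle ultrasound | Vastus lateralis images saved for processing; ultrasound images measured in Image-J | Fair inference |
| Retinal vessels | Photographs taken, then semi-automated software analysis | Fair inference |

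**3. Does the resource reason rule out masked reading?** Readers, stored images, a coding system and a key holder are all described or implied. The existing code is not masking, however: a reader who also acquired the images may recognise a number, and the visit may be visible. Fresh codes and shuffled order would be needed. The article does not say who reads the images, whether the image files carry only the code, or what staff time a masked reading would take.

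**4. Is the timing workable?** The interim assessment (section 2.7) contains none of the image measures, so only baseline (T1) and one-year (T3) images exist. They can be pooled and shuffled once T3 is complete.

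**5. How large could the effect be?** The plan gives no bias figure, so there is none to reproduce. For illustration, suppose there is no true effect and that unblinded reading shifts one arm by *d* SD. In a two-sided two-sample t-test at 0.05:

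- noncentrality: λ = d × √(n₁n₂/(n₁+n₂)), with n₁+n₂−2 degrees of freedom;
- rejection probability: P(|T| > critical value) under the noncentral t distribution.

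The 34 per group comes from section 2.9. The split of 39 and 40 is an assumed near-even division of the 79 participants who were randomised (abstract).

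| Arms | √(n₁n₂/(n₁+n₂)) | Critical t | d | λ | False-positive rate |
|---|---|---|---|---|---|
| 34 and 34 | 4.123 | 1.997 (66 df) | 0.2 | 0.825 | 12.8% |
| 34 and 34 | 4.123 | 1.997 (66 df) | 0.3 | 1.237 | 23.0% |
| 39 and 40 | 4.444 | 1.991 (77 df) | 0.2 | 0.889 | 14.2% |
| 39 and 40 | 4.444 | 1.991 (77 df) | 0.3 | 1.333 | 26.0% |

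The shifts are assumptions. The planned analysis is a repeated-measures model with a baseline covariate, not this t-test, so the figures show only the order of magnitude.

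**The case against.** The strongest reply is that the sentences around the blinding statement concern how tests are carried out. Section 3.3 says: "Measurements are standardized and performed in the same room by the same assessor at T1, T2 and T3". That describes live testing, and image readers are never mentioned. A journal article also condenses a fuller protocol, and section 2.4 refers to a standard operating procedure. How images are coded and ordered could properly be set out there, and its absence from the article is no defect. This stands as far as the missing reading procedure goes. It does not remove the point, because the article is not silent: it makes a general statement that blinding is impossible and accepts the risk.

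The limitation is openly disclosed, with a reason. That is to its credit, but disclosure does not show that the avoidable part is unavoidable.

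Three stronger readings are tempting, and the documents do not support them:

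- **That the readers do know arm and visit.** The article does not say who reads the images or what they can see. If the images are stored under the code, the restricted key already gives some protection.
- **That masked reading needs no extra staff.** The article gives no staffing for image reading. That the existing team could do it is plausible, but it is a judgement.
- **That the false-positive rate of these outcomes is 13-26%.** Those rates follow only from assumed shifts. One shift need not suit all image outcomes, and the article describes the semi-automated retinal method as highly reliable.

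Two limits also stand. Landmark palpation, probe placement and image capture would remain unblinded, so masked reading removes only part of the bias. It does nothing for the four primary endpoints: knee extension strength, reactive balance, dual task gait speed and the Agility Challenge for the Elderly.

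**Conclusion.** The point holds in limited form. Sections 2.4 and 3.3 declare assessor blinding impossible and the risk acceptable in terms broad enough to cover the reading of stored images, and the resource reason does not justify that breadth. The conclusion rests on one stated fact (offline echocardiographic analysis) and one fair inference (that muscle ultrasound and retinal images are also measured after acquisition). The actual bias cannot be sized from the documents; the calculated rates show only that modest reading shifts would matter at this sample size. The consequence is confined to secondary, mechanistic outcomes. The change is worth making because it reduces an avoidable bias at low cost, but it bears on neither the primary analysis nor the sample size.

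**What to change.** - In sections 2.4 and 3.3, restrict the statements that blinding is not possible, and that the risk is tolerable or acceptable, to live testing and image acquisition.
- Re-label all stored ultrasound, echocardiographic and fundus images with fresh random codes that hide participant, arm and visit.
- Have the existing readers read T1 and T3 images together in random order.
- Give the key to a team member who does not read images, for example the present key holder if that person is not a reader.
- If masked reading is not feasible for one of these methods, say so for that method and give the reason.

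**Cost.** A re-coding step is needed, and readings must wait until T3 images are available; any T1 images already read would have to be read again. The staff time is not known from the documents. Test procedures, sample size and the primary analysis are unchanged, and the primary endpoints gain no protection.

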### 2.5. Primary Endpoints

According to the main components of the agility training approach, we selected neuromuscular measures of strength, balance and motor performance as primary outcomes. Maximum knee extension strength is measured under isometric conditions. Therefore, participants are seated in a leg extension machine (Edition-Line, gym80, Gelsenkirchen, Germany) that is equipped with a force transducer (mechaTronic, Hamm, Germany) with a hip angle of 90° and a knee angle of 120°. Participants are instructed to push as hard and as fast as possible against a pad that is placed above their ankle joints and to keep pushing for two to three seconds, following current recommendations on instructions for strength testing [23]. Maximum strength (Fmax) and the rate of force development (RFD) are computed by the measurement/analysis software IsoTest (version 2.0, meachTronic, Hamm, Germany). Thereby, Fmax serves as a primary outcome. Participants perform three trials, of which the best two are averaged for further data analysis. This testing procedure revealed high reliability for Fmax testing (r = 0.81) [24].

Reactive balance performance is tested barefoot on a two-dimensional platform (Posturomed, Haider Bioswing, Pullenreuth, Germany) as postural sway upon perturbation. The platform, which is mounted on eight springs, is initially fixed in a stable position. A lateral shift from the neutral position for 3.6 cm is initiated. After participants have taken a stable, two-legged, shoulder-wide stance with the hands on the hips (akimbo), slight knee flexion gazing a fixed spot on the wall (at 1.5m distance, 1.75m height), the fixation is suddenly and unexpectedly released after 2 to 5 s. Participants are initially instructed to reduce the induced pendular movement as fast as possible, and remain a stable position for 10 s. An acceleration sensor (MicroSwing® 6, Haider Bioswing, Pullenreuth, Germany) captures the amplitude of the pendular movement at 50 Hz. The total sway of the platform over 10 s is calculated and reported in mm (DigiMax Posturomed, Software Version 1.0, mechaTronic, Hamm, Germany). After one familiarization trial, participants perform two trials, of which the best is used for further analysis. Failed attempts are noted as seconds until failure. Overall reliability of unexpected perturbed balance measurements was reported as good (interclass correlation (ICC) = 0.75–0.89) [25].

For assessing dual task gait speed, participants are instructed to walk an eight meter-long distance at their habitual, comfortable walking speed. Additionally, they are given a number between 100 and 110 and have to count backwards in steps of three aloud. The gait speed of three trials is measured with photoelectric time gates (DLS/F03, Sportronic, Leutenbach-Nellmersbach, Germany) and counts and errors are manually noted. The mean value of all three trials is used for data analysis. A very high reliability of this test was assessed for this test for healthy older adults (ICC = 0.93) [26].

The newly developed ACE serves as an agility-specific, functional assessment. The setup is conducted according to Lichtenstein et al. [27]. Prior to testing, participants undergo a standardized warm-up (slow and brisk walking, knee lifting, walking backwards, hip rotation). Then, the ACE is demonstrated once. Participants are instructed to pass through the course as fast as possible without running. They complete the ACE four times and the first trial serves as familiarization trial. Total time and split times of the three components of the ACE are measured with photoelectric time gates (DLS/F03, Sportronic, Leutenbach-Nellmersbach, Germany), providing high reliability values for total and split times (ICC = 0.84–0.94) and a coefficient of variation of 4%–6.7% [27].

### 2.6. Secondary Endpoints

Further secondary endpoint assessment gives further insights in the effects of agility-based training and helps us to better understand the mechanisms of possible adaptations.

#### 2.6.1. Neuromuscular Assessments

Maximal leg curl strength assessment and maximal handgrip strength measurement are conducted in line with maximal leg extension strength testing. For the leg curl test, participants are positioned prone, with a hip angle of 170° and a knee angle of 120°. They are instructed to push against a pad that is mounted above their ankle joint. Reliability data of the described testing procedure of Fmax is considered high (r= 0.94) [24]. Handgrip strength is measured using a hand dynamometer (Digimax, Hamm, Germany). Participants take a stable upright stance, placing their left hand at their hip. They are then instructed to push the handles of the dynamometer together with their right hand. The stance height is adjusted to the participants’ height. Thus, the elbow is rectangularly and the forearm parallelly positioned to the ground. The grip width is adjusted to the size of the hand. A low standard error and high reliability are reported for the handgrip strength test for seniors (standard error of measurement (SEM) = 1.89) [28].

Jump height is assessed, employing the counter movement jump (CMJ). The CMJ serves as a measure of explosive strength of the lower extremities. Participants take a stable upright shoulder-wide stance on a force plate (FP4060-15 Bertec, Columbus, OH, USA) and place their hands on their hips. They are instructed to jump as high as possible, by reactively bending and stretching their legs. After two familiarization trials, three CMJ are recorded, whereas the averaged jump heights of the two highest trials is included into further data analysis. Jump height is computed by applying the impulse method using the software MR3 (version 3.10.64, Noraxon, Cologne, Germany). The test is classified as safe and can be used to test muscle function with a coefficient of variation of 6.6% for seniors [29].

Gait speed is assessed under single and triple task conditions in line with dual task gait speed. For the single task condition, participants walk in the above-described pattern without the additional cognitive task. In the triple task condition, in addition to counting backwards, they have to successfully carry a glass in one hand that is three quarters full of water.

Muscle architecture of the lower limb is assessed via muscle ultrasound by an experienced sonographer using a Vivid iq ultrasound machine, equipped with a 5 cm 3-9 MHz linear probe (GE Healthcare Systems, Boston, MA, USA, 2018) for the right M. gastrocnemius medialis (GM) and M. soleus (SOL) or with an Esaote ultrasound system, equipped with an 11 cm 3-10 MHz linear probe (Esaote Group, Florence, Italy, 2011) for the right M. vastus lateralis (VL), respectively.

The muscle architecture of the right GM is assessed on a participant in a prone position with the knee fully extended, foot placed against a wall with a rectangular position in the ankle joint. The knee joint space is palpated and marked with a skin marker. The Achilles tendon is tracked in a distal-to-proximal direction, from its insertion at the Calcaneus bone to the myotendinous transition of the M. soleus (this length is noted as length of the Achilles tendon) to the myotendinous transition of the M. gastrocnemius medialis. The distance of that last-mentioned landmark to the knee joint space is measured and the skin is marked at 50% of that distance. The medial and the lateral edges of the GM are identified by moving the probe medially and laterally along this plane. The distance is measured and the 50% distance is marked on the skin. This point represents the center of the muscle belly at 50% GM length. Three different longitudinal images of the GM muscle are taken. Additionally, three longitudinal images are taken at the myotendinous transition of the GM, also capturing the SOL beneath. 

The muscle architecture of the right VL is assessed on a participant in a supine position with the knee fully extended [30]. The foot is placed with the sole put against a wall, resulting in a rectangular position in the ankle joint. Landmarks of the VL are palpated (greater trochanter and lateral intercondylar notch) and marked with a dermographic pencil, the distance is considered as VL length. The distal 55% VL length is measured with a flexible tape measure. The operator then positions the probe perpendicularly to the main axis of the muscle at the marked 55% VL length. The medial and the lateral edges of the VL are identified by moving the probe medially and laterally along this plane. The full distance is measured and the 50% distance is marked on the skin. This point represents the center of the muscle belly at 55% VL length. Three different longitudinal images of the VL muscle are taken and saved for processing. Since the assessment of VL ultrasound is not yet well standardized in the literature, a second method is used to locate another region of the VL used by some other authors. Therefore, the greater trochanter and the tuberositas tibiae are used as landmarks, and the 50% distance is marked on the skin. Assessment of the medial and lateral edge and the subsequent steps is the same as mentioned above. Analysis of ultrasound images is performed with the free NIH Image-J software (Version 1.52a, U.S. National Institutes of Health, Bethesda, Maryland, MD, USA). Muscle thickness, fascicle length and pennation angle will be measured. 

Reactive balance performance, as described in the primary outcomes, is also assessed with the eyes closed. Static balance is measured recording the total sway of the center of pressure (COP) on a force plate (FP4060-15 Bertec, Columbus, OH, USA) at 1000 Hz in a one-legged stance and in a tandem stance position with eyes opened. In both conditions, participants need to hold their hands on their hips, gazing a fixed point on a nearby wall (1.5m distance, 1.75m height). They are instructed to stand in the given posture as still as possible for 10 seconds. The position of the COP is captured with Digital Acquir (version 4.12, Bertec, Columbus, OH, USA) and the path length is calculated with Matlab (version R2015b, Matlab, Natick, MA, USA). To avoid frequency noise, a sixth order Butterworth filter with a low-pass cut-off frequency of 10 Hz is applied. The calculation of the total path length is achieved in meters as follows [31]:$$\mathrm{COPpathlength}=\sum_{i}^{n}\sqrt{{\left(ax_{i}-ax_{i-1}\right)}^{2}+{\left(ay_{i}-ay_{i-1}\right)}^{2}}$$

After a few seconds of familiarization, three trials are recorded, of which the best is used for further analysis. Failed attempts are noted as seconds until failure.

